## Methods: participants, interventions and outcomes

### Study setting {9}

The participants are older adults with chronic diseases from a large community setting in Hong Kong.

### Eligibility criteria {10}

Research assistants will assess the eligibility of interested participants. The inclusion criteria are Chinese adults (1) aged 60 years and above, (2) who live in the community and (3) who are diagnosed with at least one of the following chronic diseases or conditions: hypertension, hyperlipidaemia, diabetes, heart disease, COPD, chronic pain, elevated blood pressure or central obesity. To ensure capabilities in communication and decision-making for daily living, the exclusion criteria are set as follows: (1) have impaired cognitive function (a score ≤ 16th percentile in Montreal Cognitive Assessment 5-min) [48]; (2) have poor functional mobility (Timed Up and Go test ≥ 30 s) [49]; (3) are diagnosed with mental disorders (e.g. schizophrenia or depression) and/or dementia; (4) are not able to communicate in Cantonese, Mandarin, and English; and (5) have severe hearing problem that cannot be corrected by hearing aids.

### Who will take informed consents? {26a}

Consent procedures were approved by the Human Subjects Ethics Sub-committee of City University of Hong Kong. Eligible participants will receive a consent form with a summary of the study, including study procedures, risks and benefits, intervention content, voluntary participation in the study, how confidentiality will be maintained and an explanation of data collection and sharing procedures. They will be asked to provide a written informed consent by signing their names.

### Additional consent provisions for collection and use of participant data and biological specimens in ancillary studies {26b}

No additional consent provisions are needed for collecting or using biological samples. If an ancillary study will be conducted in the future, prior consent of participants to be re-contacted and informed consent will be taken for the ancillary study following approval from the Human Subjects Ethics Sub-committee of City University of Hong Kong.

### Interventions

#### Explanation for choice of comparators {6b}

Health coaching recognises the importance of individualised guidance and support in managing the self-care tasks associated with chronic disease conditions, including medication adherence, physical activity, dietary modifications and health monitoring. Whilst evidence shows the effectiveness of health coaching, most interventions are delivered by health professionals [16, 45, 50]. Whether health coaching delivered by lay health workers is still effective in enhancing individuals’ self-management competence and promoting healthy behavioural changes, particularly for community-dwelling older adults, remains uncertain. Therefore, two health coaching interventions will be compared: one delivered by lay health workers (intervention group) and another delivered by health professionals (comparison group).

#### Intervention description {11a}

The comparison and intervention groups will be assigned to a health coaching intervention. The comparison group will receive a health coaching intervention delivered by health professionals, such as nurses and dieticians, to promote a healthy lifestyle and self-management of chronic diseases. The intervention group will receive the same health intervention, except that it is delivered by lay health workers, including health promotion workers and graduates in health studies. Thus, the procedure and format of health coaching interventions remain the same across comparison and intervention groups whilst the clinical knowledge and experience of health coaches vary between them.

The health coaching intervention implemented in this study is based on effective health coaching components (e.g. motivational interviewing techniques and solution-focused goal setting) identified in systematic reviews and studies of health coaching in chronic disease management [34, 43, 51, 52]. All health coaches must complete over 100 h of training in a health coaching curriculum [53], supplemented with chronic disease-specific content (e.g. symptoms and regimens). The curriculum covers active listening and non-judgmental communication, navigating healthcare systems, setting self-management goals and motivational interviewing techniques. Although older adults may have different chronic diseases, they face similar challenges in managing their health conditions [54]. The chronic disease-specific content thus covers guidance for medication adherence, physical activity, dietary modifications and health monitoring. Due to the pragmatic nature of the study, further supervision processes will not be possible. Similar to previous studies, the health coaching intervention proceeds for 3 months [55, 56], and health coaches provide one-on-one support to older adults with chronic diseases, with a maximum caseload of 20 older adults at any given time. There will be a minimum frequency defined as one in-person or telephone contact every 6 weeks.

The health coaching intervention begins with an in-person goal-setting session at participants’ homes. During this session, participants will be presented with an individual report summarising their health status as assessed before the intervention. This report serves as a starting point for discussion. Participants are encouraged to establish one or more personally meaningful goals to work toward during the intervention. Action plans, health-related goals (e.g. lowering blood pressure) and strategies are generated by participants themselves rather than imposed by the health coaches. Subsequent sessions, either in person or over the phone, are designed to support participants’ self-determined goals by building skills in problem solving, reacting to problems, stress management, communication strategies and maintaining healthy habits. The interaction between participants and health coaches will be documented, including the date, time and relevant notes.

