#### Sample size {14}

The required sample size is estimated for one of the primary outcomes, i.e. patient activation. With reference to previous studies of patient activation interventions on chronic disease self-management [43, 61], the sample size is estimated on the basis of an effect size *f* = 0.2. Using G*Power, power analyses revealed that a total sample size of 266 is required to detect differences amongst the two intervention conditions (i.e. health coaching delivered by lay health workers vs. health professionals), using a multivariate analysis of variance with an effect size of 0.2, a power of 90% and an alpha level of 0.05, with 133 individuals in each condition. Considering the dropout rate of 30% over a period of three months, the target sample size is adjusted to 380 (with 190 individuals in each condition).

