## Statistical methods

### Statistical methods for primary and secondary outcomes {20a}

Descriptive statistics will be used to summarise participants’ baseline demographics and outcome variables throughout the study time points. Attrition analysis and randomisation tests will be carried out to test for differences in demographic and outcome variables between the intervention and comparison groups. Repeated measures ANCOVA will be conducted to examine any significant improvements in the primary and secondary outcomes across baseline and 3-month follow-up assessments whilst controlling for the effects of demographics (i.e. age, sex, education, chronic diseases) and the frequency of intervention sessions. Generalised estimating equation (GEE) analyses will be conducted to compare the primary and secondary outcomes at the 3-month follow-up between the intervention and comparison groups whilst controlling for the effects of demographics and the frequency of intervention sessions. The intention-to-treat principle will be adopted in the analyses for all the primary and secondary outcomes by imputing missing follow-up outcome data with their baseline values (i.e. assuming no change after the intervention for the primary and secondary outcomes) under the assumption of data being missing not at random. This assumption is plausible in the sense that missing data because of dropouts or non-responses are more likely amongst old-old participants with severe health problems. All statistical analyses will be conducted using R software. The treatment effect within and between the two groups will be assessed using Cohen’s *d* statistic [64].

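### Coach type is the treatment and each coach serves several participants in one arm, but the sample size assumes independent participants and the stated analysis names no coach effect or coach-level cluster

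*Protocol article*

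**What the plan says.** Under Intervention description {11a}, procedure and format are the same in both arms, and what differs is who delivers the coaching: health professionals or lay health workers. Each coach works one-on-one, "with a maximum caseload of 20 older adults at any given time". All coaches complete over 100 hours of training, and the section says that supervision beyond this will not be possible.

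Under Sample size {14}, "a total sample size of 266 is required to detect differences amongst the two intervention conditions", "with an effect size of 0.2, a power of 90% and an alpha level of 0.05". The only inflation follows: "Considering the dropout rate of 30% over a period of three months", which leads to 380 recruited, 190 per arm. No number of coaches, ICC or design effect appears.

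Under Statistical methods {20a}, generalised estimating equations (GEE) are used "to compare the primary and secondary outcomes at the 3-month follow-up between the intervention and comparison groups", controlling for demographics and frequency of sessions. Neither a coach term nor the cluster unit of the GEE is named. The sensitivity analyses under {20b} deal with missing data.

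**The concern.** Participants are randomised individually, but once allocated they share coaches, and outcomes of people with the same coach tend to be alike. In many trials such clustering is a nuisance within one arm. Here the coach is the treatment: every coach belongs to one arm, so differences between individual coaches cannot be separated from the difference between coach types except by counting coaches as a source of error.

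The trial asks whether lay workers as a class do as well as professionals, and that conclusion must hold beyond the particular people employed. If coach is left out, one very good or very weak coach can move the arm difference, the interval does not show it, and the stated power is that of a design with independent participants.

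**Working it through.** **Inputs from the protocol.** Effect size f = 0.2, power 90%, alpha 0.05, 133 analysed per arm, 30% dropout (all {14}); up to 20 concurrent participants per coach ({11a}); 5 to 10 recruits per week (Trial status). For two equal groups d = 2f = 0.4. Sidedness is not stated; two-sided is assumed.

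**Inputs assumed.** ICC by coach 0.01 to 0.05; 10 coaches per arm as the main case (190 / 20 = 9.5, if each coach serves 20 in total); equal numbers per coach.

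**Reproducing the plan's figure.** A two-group t test with d = 0.4 and independent observations has power 90.15% at 133 per arm and 89.93% at 132. So 266 reproduces, and 266 / 0.7 = 380 reproduces. The design effect is 1 and there is almost no slack: a design effect of 133 / 132 = 1.008 already brings power below 90%. With 13.3 analysed per coach that is an ICC of 0.008 / 12.3, or about 0.0006.

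**Formulas with clustering.** m = analysed per arm / coaches per arm. DE = 1 + (m − 1) × ICC. Power (normal reference) = Φ(0.4 / √(2 × DE / n) − 1.96), n per arm. Power (coach-level) = noncentral t with effective n = n / DE and 2 × coaches − 2 degrees of freedom. True type I error of a 5% test that ignores coach = 2 × (1 − Φ(1.96 / √DE)).

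Example, 10 coaches per arm, ICC 0.02: m = 133 / 10 = 13.3; DE = 1 + 12.3 × 0.02 = 1.246; 0.4 / √(2 × 1.246 / 133) = 2.922; power = Φ(0.962) = 83%. Type I error = 2 × (1 − Φ(1.756)) = 7.9%.

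Results at 133 analysed per arm:

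| Coaches per arm | ICC | DE | Power, normal | Power, coach-level df | Type I error if coach ignored |
|---|---|---|---|---|---|
| 10 | 0.01 | 1.12 | 87% | 83% | 6.4% |
| 10 | 0.02 | 1.25 | 83% | 79% | 7.9% |
| 10 | 0.05 | 1.62 | 73% | 68% | 12.3% |
| 4 | 0.01 | 1.32 | 81% | 66% | 8.8% |
| 4 | 0.02 | 1.65 | 72% | 57% | 12.6% |
| 4 | 0.05 | 2.61 | 52% | 40% | 22.5% |

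**How few coaches could there be?** At 5 to 10 recruits per week over about 13 weeks of coaching, 65 to 130 people are active at once, or about 33 to 65 per arm. Divided by 20, this needs only 2 to 4 coaches per arm at full caseload. Because the cap is on concurrent caseload, a coach's total over the year can exceed 20. Nothing in the protocol rules out many more coaches either.

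**Favourable cases.** With 5 to 7 analysed per coach and ICC 0.01, power stays near 89% (normal reference). If all 190 per arm are followed with 10 coaches per arm (m = 19), power is about 95%, 92% and 81% at ICC 0.01, 0.02 and 0.05 (normal reference).

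**The case against.** The strongest reply is that much of this rests on silence. The GEE's cluster unit is not stated, and an analysis plan that is not shown could name coach. A reader might infer that the standard errors will be too small, or that the GEE is just ordinary regression. The protocol does not establish either; both hold only if coach is left out of the analysis. This part of the reply stands.

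Second, the number of coaches and the ICC are assumptions. The caseload of 20 is a ceiling, and a small number of coaches is an inference. Common training, an identical format and goals set by the participants themselves may keep coaches alike. The lowest figures above combine few coaches with the highest ICC. This also stands, and is why a range is shown. None of it makes the correlation zero.

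Third, power is lost only if dropout is near 30%, while the section on discontinuation ({11b}) calls withdrawal unlikely. With full follow-up and a small ICC, power does exceed 90%. But 30% is the protocol's own planning figure. Replacing missing follow-up by baseline values puts 190 per arm in the data set without supplying observed outcomes.

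A reader might also infer that, in a multi-centre trial, leaving centre out of the stratification and the model makes standard errors too small. The design does not support that: participants are randomised individually, so centre is crossed with arm, and omitting it generally leaves standard errors valid or slightly conservative.

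None of this rescues the sample size. It is a published figure with its inflation explained, and it contains no allowance for coach.

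**Conclusion.** The point holds. Coaches are nested in arm by design, 266 is the figure for independent participants, and the listed adjustment terms do not include coach. At 266 analysed, practically any positive coach ICC takes power below the stated 90%. How far below cannot be read from the protocol: the 10-coach case is a working assumption, fewer coaches make both power and type I error worse, and small clusters with a small ICC cost very little.

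The power statement is the firmer half. The inflated type I error is conditional on an analysis that ignores coach, which the protocol permits by its wording but does not prescribe.

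**What to change.** - Record a coach identifier for every participant. Contacts are already documented ({11a}), and the study coordinator already gives each coach a list of assigned participants ({16c}).
- In {20a}, name coach as the cluster in the GEE with a small-sample-corrected variance, or use a mixed model with a coach random effect and Kenward-Roger degrees of freedom.
- In {14}, restate the power at 266 analysed with the actual number of coaches per arm, a stated ICC range and the same degrees of freedom as the analysis, so that the power quoted belongs to the test that will be run.
- Report the estimated coach ICC with the results.
- A centre covariate is optional.

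This changes the text and the analysis code and needs no added enrolment. It does not restore lost power: the price is wider intervals and a less favourable power statement.

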#### Criteria for discontinuing or modifying allocated intervention {11b}

Given that the procedures in this study are generally low risk, the likelihood of participants’ withdrawal or discontinuation is minimal. However, since the participants are older adults with chronic diseases, the chance of dropping out due to sudden health deterioration is still possible. The participants will be able to discontinue the intervention sessions at any point at their request.

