### Methods in analysis to handle protocol non-adherence and any statistical methods to handle missing data {20c}

Intention-to-treat analysis will be used to minimise the impact of participant dropouts and non-adherence to the protocol by analysing all participants according to their original assignment, regardless of whether they completed the study. Missing data will be imputed using statistical methods to ensure that the analysis is not biased by missing data.

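### Intention-to-treat is offered as the answer to non-adherence, but for a comparability claim it does not guard against under-delivery of coaching in both arms, and no stated analysis checks for it

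*Protocol article*

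**What the plan says.** All references are to the protocol article.

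- **Aim.** Objectives {7} has a two-part hypothesis: outcomes improve after coaching, and the improvement under lay workers is comparable to that under professionals. No margin for comparability is given.
- **Delivery.** Under Intervention description {11a}, "the health coaching intervention proceeds for 3 months" and "There will be a minimum frequency defined as one in-person or telephone contact every 6 weeks". The same section says "The health coaching intervention begins with an in-person goal-setting session at participants’ homes", and that later sessions may be in person or by telephone. Each contact is to be documented with date, time and notes. On coach oversight: "Due to the pragmatic nature of the study, further supervision processes will not be possible".
- **Stopping.** Section {11b}: "The participants will be able to discontinue the intervention sessions at any point at their request".
- **Analysis set.** Section {20a}: "The intention-to-treat principle will be adopted in the analyses for all the primary and secondary outcomes". Section {20c} presents intention-to-treat as the means of limiting the effect of dropout and non-adherence, by "analysing all participants according to their original assignment, regardless of whether they completed the study".
- **Other analyses.** In {20a}, both the repeated-measures ANCOVA and the GEE comparison adjust for how often sessions took place, and the ANCOVA tests change from baseline to 3 months. The sensitivity analyses in {20b} are complete-case and multiple-imputation analyses. The subgroup sentence there names no subgroup.

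**The concern.** In a superiority trial, non-adherence dilutes the treatment contrast and works against the hypothesis, so analysis by original assignment is conservative. When the hope is to find two arms comparable, the direction reverses: participants in either arm who receive little coaching cannot show a difference between coach types, and including them moves the estimate towards zero.

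The protocol permits low delivery. The floor is about two contacts, participants may stop when they wish, and coaches receive no further supervision. Section {20c} nevertheless treats intention-to-treat as sufficient for non-adherence, and no stated analysis looks at participants who received the coaching that the protocol defines. A conclusion that lay workers do as well as professionals could then owe something to shared under-delivery. The Abstract's Discussion would use that conclusion to advocate including lay workers in delivery.

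**Working it through.** **1. The plan's own figure.** Sample size {14} uses f = 0.2, power 90% and alpha 0.05, giving 266 in total, then 380 after 30% dropout. For two groups d = 2f = 0.40. A two-group F test on one outcome (1 and N − 2 degrees of freedom, noncentrality N × f²) needs N = 265, or 266 for equal arms, with power 0.901. Then 266 / 0.70 = 380. Both figures reproduce.

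**2. The delivery floor.** Three months is 12 to 13 weeks. One contact per 6 weeks gives 12/6 = 2.0 to 13/6 = 2.2 contacts. The text does not say whether the goal-setting visit is one of these. If it is, about one further contact meets the minimum. If it is extra, the floor is about three contacts in all.

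**3. Dilution.** Suppose a share p of each arm receives too little coaching to benefit, and coach type makes a difference D among the rest. The observed difference is (1 − p) × D. The documents give no expected delivery rate, so p is assumed, and D is set to the planning value of 0.40 SD. Power uses the normal approximation Φ(d√(n/2) − 1.96), two-sided 0.05, with n = 133 observed per arm, where √(133/2) = 8.155.

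| Assumed p | Observed d | d × 8.155 | Power | Chance of missing the difference |
|---|---|---|---|---|
| 0% | 0.40 | 3.26 | 90% | 10% |
| 10% | 0.36 | 2.94 | 84% | 16% |
| 20% | 0.32 | 2.61 | 74% | 26% |
| 30% | 0.28 | 2.28 | 63% | 37% |

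With 190 per arm and no missing outcomes, the power for 0.36, 0.32 and 0.28 SD is about 94%, 88% and 78%.

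This concerns participants with observed outcomes. Carrying baseline values forward for missing follow-up, as {20a} plans, is a separate source of dilution and is not included.

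**4. Whether the stated analyses detect it.**

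- *Session frequency as a covariate.* It is measured after randomisation and may itself depend on coach type. As a main effect it assumes the same lay-professional difference at every frequency, so it does not recover the difference among adequately coached participants.
- *Pre-post test.* It may show that neither arm improved. With no uncoached arm, it cannot separate coaching from time or regression to the mean.
- *Sensitivity analyses in {20b}.* They vary the missing-data assumption, not the coaching received.

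**The case against.** **The floor is not the schedule.** This stands. Actual contact may be well above two. Nor does the floor contradict the description of later sessions ("Subsequent sessions, either in person or over the phone, are designed to support participants" to pursue their goals): a plural is compatible with a minimum. A reader might infer that the coaching dose is inadequate. The documents do not say so, and it is not a statistical question. An analysis set defined by that floor could not show it either.

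**Delivery is not ignored.** This also stands. Contacts are logged, session frequency enters both models, and improvement from baseline is tested. A reader might infer that the results could not tell equal effectiveness from equal non-delivery, or that the arms would look alike. That goes too far: the safeguards are partial rather than absent, and the table shows attenuation under assumed values of p.

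**A per-protocol set belongs in the analysis plan.** This stands in part. Its absence alone would be no finding. But {20c} states how non-adherence is handled and why, and the reason given does not suit the aim.

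**The trial is pragmatic, and a set chosen on adherence is not randomised.** Both are true. How well each type of coach keeps participants engaged is part of the effect of coach type, and selecting on it can bias either way. That is why intention-to-treat should stay primary and the second analysis should serve only as a check. It also argues against a rule that both analyses must agree before comparability is claimed. Such a rule could not operate here in any case, because no margin is stated.

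**Conclusion.** The point holds in a limited form. For a comparability aim, the protocol is wrong to present intention-to-treat as limiting the impact of non-adherence, and no stated analysis shows whether the between-arm result persists among participants coached as defined. A 0.40 SD difference would shrink to between 0.36 and 0.28 SD if 10% to 30% of each arm were effectively uncoached, with power falling from about 90% to between 84% and 63% at 133 per arm.

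These figures assume the same share in both arms, no coach-type difference among those under-coached, and an unchanged SD. The true delivery rate is unknown and may be better. The remedy is cheap and should be adopted, but the point does not invalidate the primary analysis.

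**What to change.** 1. Keep intention-to-treat as the primary analysis.
2. Amend {20c} so that it no longer presents intention-to-treat as protecting a comparability claim against non-adherence.
3. Pre-specify one supportive between-arm analysis, adjusted for the four stratification factors (age, sex, education, number of chronic diseases), in participants who had the goal-setting visit and met the protocol's own minimum contact frequency.
4. State in {11a} whether the goal-setting visit counts towards that minimum. Without this the set is undefined. The answer is for the investigators.
5. Report by arm the number of contacts and the share of participants meeting the minimum.
6. State that comparability will be interpreted with caution if the two analyses disagree.

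The cost is some wording and one further analysis from contact dates that are already to be recorded. The supportive set will be smaller and is not protected by randomisation, so it is a consistency check only. Nothing here proposes a change to the coaching dose.
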